###### Internalized AIDS stigma

| **Internalised stigma** | | | | |
| --- | --- | --- | --- | --- |
|  | **Strongly Agree** | **Agree** | **Disagree** | **Strongly Disagree** |
| 1 It is difficult to tell other people about my HIV infection | [ ] 1. | [ ] 2. | [ ] 3. | [ ] 4. |
| 2 I am ashamed that I am HIV positive | [ ] 1. | [ ] 2. | [ ] 3. | [ ] 4. |
| 3 I sometimes feel worthless because I am HIV positive | [ ] 1. | [ ] 2. | [ ] 3. | [ ] 4. |
| 4 I feel guilty that I am HIV positive | [ ] 1. | [ ] 2. | [ ] 3. | [ ] 4. |
| 5 I hide my HIV status from others | [ ] 1. | [ ] 2. | [ ] 3. | [ ] 4. |
| 6 Being HIV positive makes me feel dirty | [ ] 1. | [ ] 2. | [ ] 3. | [ ] 4. |
| 7 It is my own fault that I am HIV positive | [ ] 1. | [ ] 2. | [ ] 3. | [ ] 4. |

#### Annex 3: Alcohol consumption

| **The Alcohol Use Disorders Identification Test (AUDIT): Interview Version-English** | | | | | | |
| --- | --- | --- | --- | --- | --- | --- |
| Dear Patient,  As part of my service I am examining lifestyle issues likely to affect the health of my patients. This information is important because it will assist me in giving the best treatment and highest possible standard of care. To help me do this, now I would like to ask you some questions about your use of alcohol beverages during the past 3 months. Your answers to these questions will be treated in strict confidence. No details of your name will be written on this questionnaire.  **Age:** ____ years **Gender:** [1] Male [2] Female **Date*:*** ____/ ____/ _______  A standard drink is: | | | | | | |
| *[figure not shown]* | *A single tot of spirits (whisky, gin & vodka)*  *(e.g., 25ml at 43%)* | *[figure not shown]* | *A small glass of liqueur or aperitif*  *(e.g., 25ml at 30%)* | | | |
| *[figure not shown]* | *1 can of ordinary beer*  *(e.g., 340ml at 5%)* | *[figure not shown]* | *1 glass of wine*  *(e.g., 120ml at 12%)* | *[figure not shown]* | *Cartoon of ordinary commercial sorghum beer*  *(e.g., 500ml at 3%)* | |
| 1. How often do you have a drink containing alcohol in the past 3 months?  Never [*skip to Qs 9-10*]……………………………….  Monthly or less.........................................................  2 to 4 times a month…………………………………..  2 to 3 times a weeks…………………………………..  4 or more times a week...……………………….......... | | (0)  (1)  (2)  (3)  (4)  [___] | 6. How often during the last 3 months have you needed a first drink in the morning to get yourself going after a heavy drinking session?  Never…………………………………………...  Less than monthly……………………………..  Monthly…………………………………………  Weekly……………………………………….....  Daily or almost daily …………………………. | | | (0)  (1)  (2)  (3)  (4)  [___] |
| 2. How many drinks containing alcohol do you have on a typical day when you are drinking?  1 or 2……………………………………..……...……  3 or 4…………………………………………..……...  5 or 6……………………………………………….....  7, 8 or 9………………………………………………...  10 or more……………………………………………... | | (0)  (1)  (2)  (3)  (4)  [___] | 7. How often during the last 3 months have you had a feeling of guilt or remorse after drinking?  Never…………………………………..……….  Less than monthly………………………..……  Monthly…………………………………….......  Weekly……………………………………........  Daily or almost daily………………………..… | | | (0)  (1)  (2)  (3)  (4)  [___] |
| 3. How often do you have (for men) five or more and (for women) four or more drinks on one occasion?  Never  Less than Monthly  Monthly  Weekly  Daily or almost daily  ***Skip to question 9 and 10 if Total Score for Qs 2 and 3 is =0*** | | (0)  (1)  (2)  (3)  (4)  [___] | 8. How often during the last 3 months have you been unable to remember what happened the night before because you had been drunk?  Never  Less than monthly  Monthly  Weekly  Daily or almost daily | | | (0)  (1)  (2)  (3)  (4)  [___] |
| 4. How often during the last 3 months have you found that you were not able to stop drinking once you had started?  Never……………………………………………………  Less than monthly……………………………………..  Monthly………………………………………………….  Weekly…………………………………………………..  Daily or almost daily…………………………………... | | (0)  (1)  (2)  (3)  (4)  [___] | 9. Have you or someone else been injured as a result of your drinking?  No……………………………………………….  Yes, but not in the last 3 months…………….  Yes, during the last 3 months……………….. | | | (0)  (2)  (4)  [___] |
| 5. How often during the last year have you failed to do what was normally expected from you because of drinking?  Never……………………………………………………  Less than monthly……………………………………..  Monthly………………………………………………….  Weekly…………………………………………………..  Daily or almost daily………………………………… | | (0)  (1)  (2)  (3)  (4)  [___] | 10. Has a relative or friend or a doctor or another health worker been concerned about your drinking or suggested you to cut down?  No……………………………………………….  Yes, but not in the last 6 months…………….  Yes, during the last 6 months……………….. | | | (0)  (2)  (4)  [___] |
| Record total of specific items here [____] | | | | | | |

**USE OF Tobacco products**

| TOB.1 Do you **currently** use one or more of the following tobacco products (cigarettes, snuff, chewing tobacco, cigars, etc.)? | **Yes** | **No** |
| --- | --- | --- |
|  | 1 | 2 |

**If ‘No’, go to next section**

TOB.2 In the past month, how often have you used one or more of the following tobacco products (cigarettes, snuff, chewing tobacco, cigars, etc.)?

| Once or twice | 1 |
| --- | --- |
| Weekly | 2 |
| Almost daily | 3 |
| Daily | 4 |

**Questionaire in Setswana Version**

#### Patient interview schedule and Demographic Characteristics

| **1. Socio-demographic data-Tswana** | | | | |
| --- | --- | --- | --- | --- |
| 1.1 O ka itlhalosa gore o wa morafe ofe? | [ ] 1. Black African  [ ] 2. Coloured | [ ] 3. Indian or Asian  [ ] 4. White | | [ ] 5. Other (specify) |
| 1.2 Ke leleme lefe leo le le dirisang ka fa gae? | [ ] 1. Afrikaans  [ ] 2. English  [ ] 3. IsiNdebele  [ ] 4. Isiswati  [ ] 5. IsiXhosa | [ ] 6. IsiZulu  [ ] 7. Sesotho sa borwa  [ ] 8. Sepedi  [ ] 9. Setswana  [ ] 10. Tshivenda | | [ ] 11. Xitsonga  [ ] 12. Other African  [ ] 13. Other European  [ ] 14. Indian language  [ ] 15. Other (specify) |
| 1.3 Dingwaga tse o di fitlheletseng |  | | | |
| 1.4 O mong? | [ ] 1. Male | [ ] 2. Female | | |
| 1.5 Maemo a gago a lenyalo? | [ ] 1. Never married  [ ] 2. Currently married  [ ] 3. Separated | [ ] 4. Divorced  [ ] 5. Widowed  [ ] 6. Living together like married partners (cohabiting) | | |
| 1.6 Dithuto tse o di fitlheletseng? Tlhopha karabo e le nngwe fela | [ ] 1. No schooling  [ ] 2. Primary education (Grade 1-6)  [ ] 3. Secondar educatuion (Grade 7-12) | | [ ] 4. Diploma(s) / Occupational certificate(s)  [ ] 5. First degree(s)/ Higher diploma(s)  [ ] 6. Honours / Master’s degree(s) and higher | |
| 1.7 Lotseno lwaka fa gae ke le le ntseng jang? | [ ] 1. Lotseno lo lo tlwaelegileng leo o duelang lekgetho.  [ ] 2. Contributions by adult family members or relatives  [ ] 3. Contributions by younger family members or relatives (<18 years)  [ ] 4. Government pensions/grants (e.g. old age pension, disability grant)  [ ] 5. Grants/donations by private welfare organizations  [ ] 6. Other (specify)_______________________________________________  [ ] 7. No income (other than social grant) | | | |
| 1.8 Ke mmano a ntseng jang a o nnang mo go one? | [ ] 1. Rural village  [ ] 2. Informal settlements  [ ] 3. Urban/Town/metropolitan area  [ ] 4. Township  [ ] 5. Farm | | | |

#### Health-related quality of life (QoL)-Setswana

###### Quality of life-SeTswana

| **Health-related quality of life** | | | | | | | | | | | | |
| --- | --- | --- | --- | --- | --- | --- | --- | --- | --- | --- | --- | --- |
| 1. O ka ipaya mo selekanong sefe ka maemo a bophelo ba gago? | [ ] 1. Tshotlego e e feteletseng | [ ] 2. Tshotlego | | | [ ] 3. Magareng | | [ ] 4. Bontle | | | [ ] 5. Bontle bo bo feteletseng | | |
| 2. O kgotsofetse go le kae ka bophelo ba gago? | [ ] 1. Go se kgotsofale go go feteletseng | [ ] 2. Go se kgotsofale | | | [ ] 3. Magareng | | [ ] 4. Go kgotsofala | | | [ ] 5. Go kgotsofala go go freteletseng | | |
| Dipotso tse di latelang di go botsa ka gore o itse go le kae ka dilo tse o di dirileng mo dibekeng tse pedi tse di fitileng. | | | | | | | | | | | | |
|  | | | Le go ka | Go le gonnye | | Mo go lekaneng | | | Go le gontsi | | | Mo go feteletseng |
| 3. Botlhoko ba mmele bo go thibela go le kae mo go direng dilo tse o tlhokang go di dira? | | | [ ] 1. | [ ] 2. | | [ ] 3. | | | [ ] 4. | | | [ ] 5. |
| 4. O tshwenyega go le kae ka mathata a mmele a a tsamaisanang le HIV/AIDS? | | | [ ] 1. | [ ] 2. | | [ ] 3. | | | [ ] 4. | | | [ ] 5. |
| 5. O tlhoka go le kae go dirisa melemo go tswelela mo letsatsing? | | | [ ] 1. | [ ] 2. | | [ ] 3. | | | [ ] 4. | | | [ ] 5. |
| 6. Botshelo bo go itumedisa go le kae? | | | [ ] 1. | [ ] 2. | | [ ] 3. | | | [ ] 4. | | | [ ] 5. |
| 7. O utlwa botshelo ba gago bo le botlhokwa go le kae? | | | [ ] 1. | [ ] 2. | | [ ] 3. | | | [ ] 4. | | | [ ] 5. |
| 8. O tshwenyega go le kae ka batho ba go kgoba ka gonne o na le bolwetse ba HIV/AIDS? | | | [ ] 1. | [ ] 2. | | [ ] 3. | | | [ ] 4. | | | [ ] 5. |
| 9. O tshoga go le kae ka bokamoso ba gago ka lebaka la HIV/AIDS? | | | [ ] 1. | [ ] 2. | | [ ] 3. | | | [ ] 4. | | | [ ] 5. |
| 10. O tshwenyega go le kae ka lefu ka lebaka la HIV/AIDS? | | | [ ] 1. | [ ] 2. | | [ ] 3. | | | [ ] 4. | | | [ ] 5. |
| 11. O kgona go le kae go reetsa ka tlhoafalo? | | | [ ] 1. | [ ] 2. | | [ ] 3. | | | [ ] 4. | | | [ ] 5. |
| 12. O ikutlwa o sireletsegile go le kae mo matsatsing a gago a bophelo? | | | [ ] 1. | [ ] 2. | | [ ] 3. | | | [ ] 4. | | | [ ] 5. |
| 13. Legae le o dulang mo go lona le tlhwekile go le kae? | | | [ ] 1. | [ ] 2. | | [ ] 3. | | | [ ] 4. | | | [ ] 5. |
|  | | | Le go ka | Go le gonnye | | Mo go lekaneng | | | Go le gontsi | | | Mo go feeletseng |
| 14. A o na le maikatlapelo a a lekaneng go tshela letsatsi le letsatsi? | | | [ ] 1. | [ ] 2. | | [ ] 3. | | | [ ] 4. | | | [ ] 5. |
| 15. O kgona go amogela seemo se o lebegang ka sona? | | | [ ] 1. | [ ] 2. | | [ ] 3. | | | [ ] 4. | | | [ ] 5. |
| 16. O na le madi a a lekaneng go fitlhelela ditlhokego tsa gago? | | | [ ] 1. | [ ] 2. | | [ ] 3. | | | [ ] 4. | | | [ ] 5. |
| 17. O ikutlwa o amogetswe go le kaego le kae ke batho ba ba itseng seemo sa gago sa HIV/AIDS? | | | [ ] 1. | [ ] 2. | | [ ] 3. | | | [ ] 4. | | | [ ] 5. |
| 18. Kitso e e tlhokagalang e teng go le kae mo matsatsing a gago a bophelo? | | | [ ] 1. | [ ] 2. | | [ ] 3. | | | [ ] 4. | | | [ ] 5. |
| 19. O kgona go le kae go fitlhelela sebaka sa go iketla? | | | [ ] 1. | [ ] 2. | | [ ] 3. | | | [ ] 4. | | | [ ] 5. |
| 20. O kgona jang go tswelela? | | | [ ] 1. | [ ] 2. | | [ ] 3. | | | [ ] 4. | | | [ ] 5. |
|  | | | Go se kgotsofale mo go feteletseng | Go se kgotsofale | | Magareng | | | Go kgotsofala | | | Go kgotsofala go go feteletseng |
| 21. O kgotsofala go le kae ka boroko ba gago? | | | [ ] 1. | [ ] 2. | | [ ] 3. | | | [ ] 4. | | | [ ] 5. |
| 22. O kgotsofala go le kae ka mokgwa o o kgonang go dira ditiro tsa gago tsa letsatsi? | | | [ ] 1. | [ ] 2. | | [ ] 3. | | | [ ] 4. | | | [ ] 5. |
| 23. O kgotsofala go le kae ka bokgone ba gago ba go dira ditiro tsa gago tsa letsatsi? ? | | | [ ] 1. | [ ] 2. | | [ ] 3. | | | [ ] 4. | | | [ ] 5. |
| 24. O kgotsofala go le kae ka ga wena? | | | [ ] 1. | [ ] 2. | | [ ] 3. | | | [ ] 4. | | | [ ] 5. |
| 25. O kgotsofala go le kae ka bokgotsi ba gago? | | | [ ] 1. | [ ] 2. | | [ ] 3. | | | [ ] 4. | | | [ ] 5. |
| 26. O kgotsofala go le kae ka bophelo ba gago ba thobalano? | | | [ ] 1. | [ ] 2. | | [ ] 3. | | | [ ] 4. | | | [ ] 5. |
| 27. O kgotsofala go le kae ka kemonokeng e metswalle ya gago e go neang yone? | | | [ ] 1. | [ ] 2. | | [ ] 3. | | | [ ] 4. | | | [ ] 5. |
| 28. O kgotsofala go le kae ka maemo a o dulang mo go ona? | | | [ ] 1. | [ ] 2. | | [ ] 3. | | | [ ] 4. | | | [ ] 5. |
| 29. O kgotsofala go le kae ka go fitlhelela tsa pholo? | | | [ ] 1. | [ ] 2. | | [ ] 3. | | | [ ] 4. | | | [ ] 5. |
| 30. O kgotsofala go le kae ka senamelwa se o se dirisang? | | | [ ] 1. | [ ] 2. | | [ ] 3. | | | [ ] 4. | | | [ ] 5. |
| Dipotso tse di latelang di botsa go le kae ka dilo tse o di dirileng mo dibeke tse pedi tse di fitileng. | | | | | | | | | | | | |
| 31. Ke ga kae o ikutlwa o na le letshogo e bile moya wa gago o le ko tlase? | [ ] 1. Le go ka | [ ] 2. Go le gonnye | | | [ ] 3. Go le gontsi | | | [ ]4.Go le gontsi thata | | | [ ] 5. Le go ka | |

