#### Annex 2: Health-related quality of life (QoL)

###### Quality of life

| **Health-related quality of life** | | | | | | | | | | | | |
| --- | --- | --- | --- | --- | --- | --- | --- | --- | --- | --- | --- | --- |
| 1. How would you rate your quality of life? | [ ] 1. Very poor | [ ] 2. Poor | | | [ ] 3. Neither poor nor good | | [ ] 4. Good | | | [ ] 5. Very good | | |
| 2 How satisfied are you with your health? | [ ] 1. Very dissatisfied | [ ] 2. Dissatisfied | | | [ ] 3. Neither satisfied nor dissatisfied | | [ ] 4. Satisfied | | | [ ] 5. Very satisfied | | |
| The following questions ask about **how much** you have experienced certain things in the last two weeks. | | | | | | | | | | | | |
|  | | | **Not at all** | **A little** | | **A moderate amount** | | | **Very much** | | | **An extreme amount** |
| 3 To what extent does physical pain prevent you from doing what you need to do? | | | [ ] 1. | [ ] 2. | | [ ] 3. | | | [ ] 4. | | | [ ] 5. |
| 4 How much are you bothered by physical problems related to HIV/AIDS? | | | [ ] 1. | [ ] 2. | | [ ] 3. | | | [ ] 4. | | | [ ] 5. |
| 5 How much do you need any medical treatment to function in your daily life? | | | [ ] 1. | [ ] 2. | | [ ] 3. | | | [ ] 4. | | | [ ] 5. |
| 6 How much do you enjoy life? | | | [ ] 1. | [ ] 2. | | [ ] 3. | | | [ ] 4. | | | [ ] 5. |
| 7 To what extent do you feel your life to be meaningful? | | | [ ] 1. | [ ] 2. | | [ ] 3. | | | [ ] 4. | | | [ ] 5. |
| 8 To what extent are you bothered by people blaming you for having HIV/AIDS? | | | [ ] 1. | [ ] 2. | | [ ] 3. | | | [ ] 4. | | | [ ] 5. |
| 9 How much do you fear for the future because of HIV/AIDS? | | | [ ] 1. | [ ] 2. | | [ ] 3. | | | [ ] 4. | | | [ ] 5. |
| 10 How much do you worry about death because of HIV/AIDS? | | | [ ] 1. | [ ] 2. | | [ ] 3. | | | [ ] 4. | | | [ ] 5. |
| 11 How well are you able to concentrate? | | | [ ] 1. | [ ] 2. | | [ ] 3. | | | [ ] 4. | | | [ ] 5. |
| 12 How safe do you feel in your daily life? | | | [ ] 1. | [ ] 2. | | [ ] 3. | | | [ ] 4. | | | [ ] 5. |
| 13 How healthy is your physical environment? | | | [ ] 1. | [ ] 2. | | [ ] 3. | | | [ ] 4. | | | [ ] 5. |
|  | | | **Not at all** | **A little** | | **Moderately** | | | **Mostly** | | | **Completely** |
| 14 Do you have enough energy for everyday life? | | | [ ] 1. | [ ] 2. | | [ ] 3. | | | [ ] 4. | | | [ ] 5. |
| 15 Are you able to accept your bodily appearance? | | | [ ] 1. | [ ] 2. | | [ ] 3. | | | [ ] 4. | | | [ ] 5. |

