| 16 Have you got enough money to meet your needs? | | | [ ] 1. | [ ] 2. | | [ ] 3. | | | [ ] 4. | | | [ ] 5. |
| 17 To what extent do you feel accepted by the people you know, whether or not they are aware of your HIV/AIDS? | | | [ ] 1. | [ ] 2. | | [ ] 3. | | | [ ] 4. | | | [ ] 5. |
| 18 How available to you is the information that you need in your day-to-day life? | | | [ ] 1. | [ ] 2. | | [ ] 3. | | | [ ] 4. | | | [ ] 5. |
| 19 To what extent do you have the opportunity for leisure activities? | | | [ ] 1. | [ ] 2. | | [ ] 3. | | | [ ] 4. | | | [ ] 5. |
| 20 How well are you able to get around? | | | [ ] 1. | [ ] 2. | | [ ] 3. | | | [ ] 4. | | | [ ] 5. |
|  | | | **Very dissatisfied** | **Dissatisfied** | | **Neither satisfied nor dissatisfied** | | | **Satisfied** | | | **Very satisfied** |
| 21 How satisfied are you with your sleep? | | | [ ] 1. | [ ] 2. | | [ ] 3. | | | [ ] 4. | | | [ ] 5. |
| 22 How satisfied are you with your ability to perform your daily activities? | | | [ ] 1. | [ ] 2. | | [ ] 3. | | | [ ] 4. | | | [ ] 5. |
| 23 How satisfied are you with your capacity to work? | | | [ ] 1. | [ ] 2. | | [ ] 3. | | | [ ] 4. | | | [ ] 5. |
| 24 How satisfied are you with yourself? | | | [ ] 1. | [ ] 2. | | [ ] 3. | | | [ ] 4. | | | [ ] 5. |
| 25 How satisfied are you with your personal relationships? | | | [ ] 1. | [ ] 2. | | [ ] 3. | | | [ ] 4. | | | [ ] 5. |
| 26 How satisfied are you with your sex life? | | | [ ] 1. | [ ] 2. | | [ ] 3. | | | [ ] 4. | | | [ ] 5. |
| 27 How satisfied are you with the support you get from your friends? | | | [ ] 1. | [ ] 2. | | [ ] 3. | | | [ ] 4. | | | [ ] 5. |
| 28 How satisfied are you with the condition of your living space? | | | [ ] 1. | [ ] 2. | | [ ] 3. | | | [ ] 4. | | | [ ] 5. |
| 29 How satisfied are you with your access to health services? | | | [ ] 1. | [ ] 2. | | [ ] 3. | | | [ ] 4. | | | [ ] 5. |
| 30 How satisfied are you with your transport? | | | [ ] 1. | [ ] 2. | | [ ] 3. | | | [ ] 4. | | | [ ] 5. |
| **The following question refers to how often you have felt or experienced certain things in the last two weeks.** | | | | | | | | | | | | |
| 31 How often do you have negative feelings such as depressed mood, despair, anxiety? | [ ] 1. Never | [ ] 2. Seldom | | | [ ] 3. Quite often | | | [ ] 4.Very often | | | [ ] 5. Never | |

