###### Sexual Behaviour-Setswana

| **Sexual behaviour** | | | | | | |
| --- | --- | --- | --- | --- | --- | --- |
| Nagana sentle ka ga dikgwedi tse 3 tse di fitileng mme o tlhophe karabo ya gago. | | | | | | |
| 1. O ne wa tsena mo thobalanong mo kgweding tse tharo tse di fitileng? | Ee [ ] | Nya [ ] | Ga o re nya, e ya ko potso ya bolesome | | | |
| 2. O robalane le borre ba le bakae mo kgweding tse tharo tse di fitileng? | 0 | 1 | 2 | 3 | 4 | 5 kgotsa ba go feta |
| 3. O robalane le bomme ba le bakae mo kgweding tse tharo tse di fitileng? | 0 | 1 | 2 | 3 | 4 | 5 kgotsa ba go feta |

Jaanong nagana sentle ka ga dikgwedi tse 3 tse di fitileng.

Mo kgweding tse 3 tse di fitileng-Ke makgetho a le makae……

| 4. O tsene mo thobalanong ka ntle le go dirisa kgotlhopo? | 0 | 1-2 | 3-5 | 6-10 | 11-20 | 21-30 | 31-40 | 41 kgotsa ba go feta |
| --- | --- | --- | --- | --- | --- | --- | --- | --- |
| 5. O tsene mo thobalanong o dirisa kgotlhopo? | 0 | 1-2 | 3-5 | 6-10 | 11-20 | 21-30 | 31-40 | 41 kgotsa ba go feta |
| 6. O tsene mo thobalanong o nwele bojalwa? | 0 | 1-2 | 3-5 | 6-10 | 11-20 | 21-30 | 31-40 | 41 kgotsa ba go feta |
| 7. Molekane wa gago a nwele bojalwa pele le robalana? | 0 | 1-2 | 3-5 | 6-10 | 11-20 | 21-30 | 31-40 | 41 kgotsa ba go feta |
| 8. O dirisitse diritibatsi pele ga thobalano? | 0 | 1-2 | 3-5 | 6-10 | 11-20 | 21-30 | 31-40 | 41 kgotsa ba go feta |
| 9. Molekane wa gago a dirisitse diritibatsi pele ga thobalano? | 0 | 1-2 | 3-5 | 6-10 | 11-20 | 21-30 | 31-40 | 41 kgotsa ba go feta |

| 10. O ne wa se dirise kgolhopo le molekane yo o sa itseng maemo a gagwe a HIV | [ ] 1. Ee [ ] 2. Nya |
| --- | --- |
| **11. Mo kgweding tse 3 tse di fitileng –Ke itsisitse** Molekane wa bofelo o ke neng ka tsena mo thobalanong le ena ka maemo a me a HIV | [ ] 1. Ee [ ] 2. Nya |

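### Setswana quality-of-life items 17 and 23, and apparently items 13 and 20, ask something different from their English counterparts, so the score does not mean the same thing in both languages

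*Protocol*

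**What the plan says.** Objectives 4 and 5 list quality of life among the outcomes compared between arms at 3 and 12 months, as levels and as changes. Objective 3 compares it over time. The section on health-related quality of life names the WHOQoL-HIVBREF, taken at baseline and at each follow-up visit. The section on alcohol consumption says that all questionnaires are given in English or Tswana. The section on reliability and validity says that all instruments are standard and already validated, and makes no exception for translated versions.

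Annex 2 prints the English form and the Setswana form follows later, each with 31 items. The pairs that matter most are:

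- Item 17. English: "To what extent do you feel accepted by the people you know, whether or not they are aware of your HIV/AIDS". Setswana: acceptance "ke batho ba ba itseng seemo sa gago sa HIV/AIDS".
- Item 23. English: "How satisfied are you with your capacity to work". Setswana: satisfaction "ka bokgone ba gago ba go dira ditiro tsa gago tsa letsatsi".
- Item 13. English: "How healthy is your physical environment". Setswana: "Legae le o dulang mo go lona le tlhwekile go le kae".
- Item 20. The English asks about getting around. The Setswana uses the verb *tswelela*.

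**The concern.** The two forms carry the same item numbers and the same 1 to 5 coding, so their answers will be treated as one measurement. If an item asks different things in the two languages, its pooled value mixes two constructs. A patient's level on it then depends partly on the language of interview.

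Item 17 is the most serious case. The protocol expects some patients not to have disclosed: stigma items 1 and 5 ask about difficulty in telling others and about hiding one's status, and the sexual behaviour form asks about recent disclosure. For a patient who has told nobody, the Setswana item has no clear group of people to refer to, and the response scale has no not-applicable option. If a patient discloses during follow-up, the group the item refers to changes, so a change score need not compare like with like.

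For item 23, a Setswana respondent is in effect asked about daily activities twice, and work is not distinctly addressed. This cannot be repaired at analysis, because the question was not put.

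**Working it through.** No figure in the protocol needs reproducing. The check sets the two forms side by side and uses the protocol's other parallel English and Setswana text to test the key words.

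**Item 17.** The English reference group is "accepted by the people you know, whether or not they are aware of your HIV/AIDS". The Setswana describes the people with the verb *itseng* (know) and their object is the patient's status: "ke batho ba ba itseng seemo sa gago sa HIV/AIDS". The Setswana sexual behaviour form, item 10, uses the same verb in the negative, "le molekane yo o sa itseng maemo a gagwe a HIV", where the English speaks of a partner of unknown status. The Setswana item 17 has nothing corresponding to the English clause that includes people unaware of the status. This mismatch is firm.

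**Item 23.** Setswana items 22 and 23 share their last seven words, from *go dira* to *letsatsi*. In item 22 that ending renders the English daily activities. In item 23 it stands where the English has capacity to work. The words before it differ (*bokgone* in item 23, a different construction in item 22), so the item is a near-duplicate, not a verbatim repeat. It is firm that work is not distinctly asked.

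**Item 20.** The verb *tswelela* renders get going in the last item of the Setswana CES-D and renders function in quality-of-life item 5. Neither is mobility. Because the protocol itself uses the verb in two senses, the exact reading needs a Setswana speaker.

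**Item 13.** *Legae* points to the home: the related form *gae* renders household in demographic item 1.2, and *dulang* recurs in item 28, where the English is about living space. So the narrowing from environment to home has internal support. Reading *tlhwekile* as clean has no parallel in the protocol and needs confirmation.

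**Size.**

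- Firm items only: 2/31 = 6.5%.
- All four items: 4/31 = 12.9%.

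The share *s* of interviews held in Setswana is not stated, so I vary it. Assume a simple item sum, equal weight and equal effect on every item, and, as an extreme, no intended signal at all from the *k* affected items in Setswana. The effect retained is then 1 − *s* × *k*/31:

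| *s* | *k* = 2 | *k* = 4 |
|---|---|---|
| 25% | 98.4% | 96.8% |
| 50% | 96.8% | 93.5% |
| 75% | 95.2% | 90.3% |
| 100% | 93.5% | 87.1% |

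The protocol defines no 31-item sum, so the table only indicates scale. A score built from fewer items would be affected more if it contained one of these four.

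**The case against.** Several points on the other side have force.

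- **No bias between arms.** A reader might infer that the mismatch distorts the treatment comparison. The protocol does not support that: both randomised arms use the same two forms. This objection stands.
- **Item 17 can still be answered.** A reader might infer that patients who have told nobody cannot answer it or cannot be scored. The form is administered by an interviewer, the scale includes a lowest category, and clinic staff know the patient's status. An answer will normally be recorded. What is in doubt is its meaning.
- **A maximum shift is not a magnitude.** Four items with a range of 4 points each give 4 × 4 = 16 raw points, and a reader might take this as the possible error. It would require all four items to move across the whole scale in the same direction through wording alone, and nothing in the protocol supports that.
- **Items 13 and 20 depend on reading Setswana.** This stands in part. They are flagged for confirmation, and the statement that mobility is wholly unmeasured would go further than the text proves.
- **Quality of life is one outcome among several.** The sample size rests on adherence, and the repeated-measures ANOVA is specified for the alcohol score. This limits the consequence but does not remove it, because quality of life is in the objectives and the hypotheses.
- **A pre-test is planned.** The timetable and budget include one, but neither mentions back-translation or a check of equivalence between languages.

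An analysis plan might deal with interview language. It could not recover a question that was not asked.

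**Conclusion.** The point holds for the wording of the printed instrument. Items 17 and 23 differ between languages on the evidence of the protocol's own parallel text. Items 13 and 20 appear to differ, subject to a Setswana speaker's confirmation. Between 6.5% and 12.9% of the items are affected.

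The consequences are dilution of the affected items, quality-of-life levels that are not comparable across languages, and an item 17 with no clear referent for patients who have not disclosed. The protocol's blanket claim of validity cannot be carried over to the Setswana form as printed.

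Under the extreme illustration above, with assumed Setswana shares of 25% to 100%, an item-sum effect would keep 87.1% to 98.4% of its size. The loss is modest. If nearly all interviews were in one language, the mixing of languages would matter little, but if that language were Setswana the content fault in the items would remain. The correction should be made because it is cheap and its effect on the arm comparison is limited to dilution, not bias.

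**What to change.** Before printing, revise Setswana items 17 and 23 to match the English. Item 17 should refer to people the patient knows, regardless of whether they are aware of the status. Item 23 should refer to work. Have a Setswana speaker confirm items 13 and 20 and correct them if the mismatch is upheld. Add independent back-translation of the revised items to the questionnaire pre-test, and state in the protocol that it was done.

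If any interviews have already used the annexed form, record the language of interview at each visit. Then report quality of life by language, or add a sensitivity analysis that omits the affected items for all patients in both languages. Omitting them only for patients interviewed on the uncorrected form is tempting but would itself make scores non-comparable: in a raw sum, those patients would have 31 − 4 = 27 items against 31 for the rest.

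The cost before fieldwork is up to four lines of text plus back-translation of those lines. Pre-testing and printing are already in the timetable for August 2011 and in the budget. After recruitment, the missing content cannot be recovered for visits already held in Setswana.
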